### Oversight and monitoring

2.10

Specific protocols will be implemented to safeguard data and participant well-being. The principal investigators will collaborate with a physician who leads the non-invasive and precision neuromodulation institute to monitor and evaluate the study's progress and safety measures. Despite the minimal reported side effects, patients will undergo a 14-day monitoring period following the procedure. The operation will be halted if the patient reports any localized signs or symptoms of infection. The analysis of the study will utilize information gathered prior to the conclusion of the intervention. To ensure participant safety, all individuals who completed the intervention phase will receive follow-up phone calls for a week after completion. An Independent Safety Monitor, who is the ethics committee secretary that approved the study, will receive and review biannual progress reports. These reports cover participant recruitment, retention/attrition, and adverse events. At the conclusion of the study, a comprehensive report will be prepared detailing and summarizing the adverse events. The concluding report will include explanations provided by the study participants who chose to withdraw. The reasons behind their withdrawal will be examined and contrasted with the initial expectations of the researchers to uncover the patterns and possible factors influencing these decisions. Furthermore, an evaluation will be conducted to predict which participants might leave the study early, with the goal of developing strategies to mitigate this and ensure the reliability of results. The Data Safety Monitoring Plan requires that any serious adverse events be reported to the ethics committee within a 48-hour timeframe. Should an unexpected serious adverse event pose an increased risk to participants, the study will be suspended if the independent safety monitor determines it is necessary due to the frequency or severity of the events.

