### Sample size

2.6

The required sample size was determined using GPower® software (Franz Faul, Universität Kiel, Kiel, Germany), version 3.1.9.2. A preliminary sample of 46 subjects, divided into two groups of 23 participants each, was established for the intervention design. The primary variable (EMG output) was used for statistical analysis through repeated measures ANOVA. Cohen's effect size was set at 0.357 based on a previous study examining using surface EMG recordings as their primary outcome (41). The calculation incorporated a statistical power of 0.95, an alpha level of 0.05, and two intervention groups. To account for potential dropouts during treatment follow-up (estimated at 15%), an additional 3 participants were added to each group. This resulted in a total of 54 participants, with 27 per group. The chosen effect size, exceeding 0.357, is classified as “moderate” (42). If a greater percent of participants does not follow their planned treatment protocol (dropouts, non-adherence to treatment, or missing results), an “intention-to-treat” analysis will be conducted.

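### Post-treatment safety calls are tied to completing the intervention phase, so participants who stop tDCS or sham early have no stated calls and late adverse events may be sought unequally

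*Protocol article*

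**What the plan says.** All the safety contact rules are in section 2.10, Oversight and monitoring, of the protocol article.

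- **Calls.** The stated purpose is participant safety, and the rule is that "all individuals who completed the intervention phase will receive follow-up phone calls for a week after completion".
- **Monitoring period.** A little earlier the section says that "patients will undergo a 14-day monitoring period following the procedure". It does not say which procedure is meant or how contact is made.
- **Reports.** Of the biannual reports to the safety monitor it says: "These reports cover participant recruitment, retention/attrition, and adverse events". At the end of the study "a comprehensive report will be prepared detailing and summarizing the adverse events". Serious events go to the ethics committee within 48 hours. None of this is limited to completers.
- **Withdrawals.** "The concluding report will include explanations provided by the study participants who chose to withdraw".
- **Data window.** "The analysis of the study will utilize information gathered prior to the conclusion of the intervention".

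Section 2.6, Sample size, plans for loss with the words "To account for potential dropouts during treatment follow-up (estimated at 15" (a percentage) and arrives at 54 participants, 27 per group.

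**The concern.** Completion occurs after randomisation and can depend on how well the stimulation is tolerated, and so on the arm. A safety contact conditional on it searches for late events mainly in those who got through the course. A participant who stops partway has neither an entitlement to the calls nor a date from which they would run. The section itself foresees halting when signs of infection are reported, so it creates non-completers who have had a safety problem and fall outside the calls.

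At stake is the completeness of the adverse-event summary for events that appear or persist after stopping. If more participants stop in one arm than in the other, the intensity of the search would differ between arms too. With 27 per arm, one missed event shifts that arm's rate by 1/27 = 3.7 percentage points, so a few missed events would be visible in a by-arm table.

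**Working it through.** No figure in the article depends on this sentence, so there is none to reproduce. The check is a reading of the provisions side by side, followed by a calculation of scale.

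**1. Does another provision cover early stoppers after their last session?**

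| Provision | Limited to completers? | Actively seeks events after early stopping? |
|---|---|---|
| One-week calls (2.10) | Yes | No, as written |
| 14-day monitoring (2.10) | No | Unclear: it could follow surgery, each session or the last session |
| Biannual and final reports (2.10) | No | No: they report what is already known |
| 48-hour reporting (2.10) | No | No: serious events only, once known |
| Withdrawal explanations (2.10) | Not applicable | No: they give reasons for leaving, from those who chose to leave |
| Visits at 1, 2, 3 and 6 months (2.4); 72 rehabilitation sessions (2.7.1) | No | Possibly, if the participant still attends; not described as safety contacts |

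No provision clearly closes the gap, but several may close part of it.

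**2. What counts as the intervention phase?** Section 2.7.1 gives 16 stimulation sessions over 8 weeks and 72 rehabilitation sessions over 24 weeks. If the phase is the stimulation course, the calls follow week 8. If it is the whole programme, and stimulation starts with rehabilitation, the calls come 24 − 8 = 16 weeks after stimulation ends. On that reading a participant who received all 16 stimulation sessions but left rehabilitation gets no calls.

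**3. How many participants?** Inputs: 15% dropout and N = 54 (2.6). 0.15 × 54 = 8.1, about 8 in total and about 4 per arm if the arms are equal. This is an upper figure if the 15% is taken to include all early stopping. It covers all loss during follow-up, and under the 8-week reading those lost after week 8 count as completers and are called.

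**4. How far could the observed event rate fall short?** The article gives no event rates, so these are assumptions. Let a be the rate in 46 completers, s the rate in 8 early stoppers, and m the share of early stoppers' events that is missed.

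- True rate = (46a + 8s)/54
- Observed rate = (46a + 8s(1 − m))/54
- Shortfall = 8sm/54

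With a = 10% and s = 30%, the true rate is (4.6 + 2.4)/54 = 13.0%. The observed rate is:

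- m = 0: 13.0%
- m = 0.5: (4.6 + 1.2)/54 = 10.7%
- m = 1: 4.6/54 = 8.5%

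The shortfall does not depend on a. For s from 10% to 50% and m from 0 to 1 it runs from 0 to 8 × 0.50/54 = 7.4 percentage points. The upper end requires every event in early stoppers to be missed.

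**The case against.** A reader might infer that the calls are the only active safety contact after treatment, and that the safety summary is therefore biased toward tolerability. The documents do not support that.

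- The 14-day monitoring applies to patients generally and lasts twice as long as the calls.
- The adverse-event and serious-event reports are not restricted to completers. An event that caused someone to stop arises before any call window and can be recorded when it happens.
- Stopping stimulation is not the same as leaving the trial. Someone who stops stimulation but continues rehabilitation and visits is seen more often than a week of calls would provide.
- The article specifies no between-arm safety comparison that could be called biased.
- Participants who have left and cannot be reached would gain nothing from a wider call rule.

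These points stand, and they reduce the concern to a risk affecting late or persisting events.

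It can also be said that a condensed article leaves follow-up after discontinuation to the Data Safety Monitoring Plan, which section 2.10 mentions and which is not shown. That plan may indeed hold a wider rule. But the article does more than leave the matter open: it states who is called and counts the week from completion. Staff following that sentence would have no instruction to call anyone else.

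**Conclusion.** The point holds as a risk of ascertainment that depends on completion and possibly on arm. Early stoppers have no stated post-treatment calls, and the one provision that might replace the calls is ambiguous. At most about 8 of 54 participants are affected, on the assumption that the planned 15% includes all early stopping. The loss in the observed event rate lies anywhere from zero, if other routes capture the events, to about 7.4 percentage points under the most unfavourable of the assumed rates. The article does not show where in that range the trial would fall, so neither a bias nor its direction between arms is established. The change is still worth making, because it is small and removes the dependence on completion.

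**What to change.** In section 2.10:

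1. Reword the call sentence so that every randomised participant who received at least one active or sham session gets the same calls, counted from that participant's last session whether or not the course was completed.
2. State that adverse events will be summarised by arm in that population.
3. Define the procedure that starts the 14-day monitoring and define the intervention phase (8-week stimulation course or 24-week programme), so that the monitoring period and the one-week calls can be reconciled.
4. Reconcile the sentence on the data window, which read literally would leave what the calls find out of the analysis.

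The cost is a few sentences and about 8 extra short call series at most, with no new visit. Some participants who withdrew may not be reachable; reporting how many were reached in each arm would show how much of the gap remains.

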#### Data collection

2.10.1

Patient medical information will be entered directly into a secure computer system located at the evaluation sites. Each patient will receive their own unique identifier to anonymize data. To enable data sharing among researchers for further analysis, an Excel file containing only unique patient identifiers will be distributed. This method safeguards the confidentiality and security of information.

#### Statistical analysis

2.10.2

##### Baseline characteristics

2.10.2.1

To evaluate demographic baseline measures across intervention groups, comparisons will be conducted using analysis of variance (ANOVA) or chi-square tests (i.e., NIBS + Protocol_RHB_ and ShamNIBS + Protocol_RHB_) to identify statistically significant differences between groups (*p* > 0.05).

##### Analysis of the outcome measures

2.10.2.2

A per-protocol analysis will be performed in accordance with the CONSORT guidelines for reporting randomized controlled trials. The Kolmogorov–Smirnov test will be utilized to verify the normality assumption, and the Levene test will be used to evaluate the homogeneity of variances. To examine the effects of tDCS combined with exercise-based rehabilitation on patients undergoing ACL reconstruction, repeated measures ANOVA will be applied, with experimental groups as factors and Bonferroni corrections for *post hoc* analysis. Comparisons within and between groups for both primary and secondary outcomes will assess time, group, and interaction effects. Results will be expressed as mean differences (MD) with 95% confidence intervals (CI95%). The effect size (ES) will be calculated using Cohen's d coefficient. All statistical analyses will be conducted using SPSS 24 software (IBM Inc., Chicago, Illinois, USA). If there are participant dropouts or if the statistical power is below 80%, an intention-to-treat analysis will be implemented (78).

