### Program feasibility and safety: attendance and compliance with protocol

2.9

Several factors influence the adherence of patients with ACL injuries to their exercise regimens. Improving a patient's ability to complete a rehabilitation program, especially home exercises, can be facilitated by considering social and environmental factors that enhance adherence and compliance (74). Furthermore, following the recommended guidelines for return-to-sport clearance after ACL reconstruction is essential for effective rehabilitation (75). Key factors that impact attendance at physiotherapy appointments and participation in sessions include therapist support, rehabilitation setting, and exercise progression (76). For this study, protocol adherence will be measured by calculating the percentage of patients who complete the assessments following established methods from previous research (77). In the initial stages, individualized training will be provided to ensure treatment plan compliance and minimize the risk of adverse effects.

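### Per-protocol is the only unconditional analysis, intention-to-treat hangs on two unharmonised conditions, and the analysis that decides the trial is not fixed

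*Protocol article*

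**What the plan says.** The Introduction expects tDCS plus rehabilitation to do better than sham plus rehabilitation, so this is a superiority comparison.

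Three places in the protocol article bear on who is analysed:

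- **Section 2.10.2.2 (Analysis of the outcome measures), the default:** "A per-protocol analysis will be performed in accordance with the CONSORT guidelines for reporting randomized controlled trials". No other analysis set is named without a condition.
- **Section 2.10.2.2, the condition:** "If there are participant dropouts or if the statistical power is below 80%, an intention-to-treat analysis will be implemented". How and when power would be assessed is not stated.
- **Section 2.6 (Sample size):** "If a greater percent of participants does not follow their planned treatment protocol (dropouts, non-adherence to treatment, or missing results" is the condition, and the consequence is that "an “intention-to-treat” analysis will be conducted". The sentence follows the 15% dropout estimate, so the comparison is most naturally with that 15%.

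Section 2.10 (Oversight and monitoring) adds a sentence that bears on which data count: "The analysis of the study will utilize information gathered prior to the conclusion of the intervention".

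**The concern.** In a superiority trial, the comparison that randomisation protects is the one between all randomised participants in their assigned arms. A per-protocol set removes people for what they did after randomisation. If the reasons differ between arms, the groups compared are no longer those that were randomised. Here that set is the default, and ITT enters only under conditions that are assessed as the trial runs and that differ between two sections.

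The trial could therefore end with a per-protocol result and an ITT result and no prior rule on which one counts. If they disagree, the choice would be made with both in view. The undefined power condition adds a route by which the outcome result itself could call for a change of analysis set.

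**Working it through.** **Inputs.** From section 2.6: 46 participants (23 per group) before dropout, 15% dropout, 54 (27 per group) after, alpha 0.05. From section 2.4: four scheduled visits. Assumptions made here: participants drop out independently, and the section 2.6 condition means more than 15% of 54.

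**The plan's own figure.** 46 / (1 − 0.15) = 54.1, which agrees with 54. The stated addition of 3 per group would give 23 + 3 = 26 per group, or 52. That is a separate slip, and 52 is carried below as a check. The 46 cannot be reproduced, because the number of measurements and their correlation in the power calculation are not stated. Nothing below depends on how it was derived.

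**Step 1: how often each condition is met.**

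Any dropout: 1 − (1 − q)^54. At q = 0.15, 0.85^54 = 0.00015, so the probability is 0.9998.

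More than 15%: 0.15 × 54 = 8.1, so 9 or more are needed. P(X ≥ 9) for X ~ Binomial(54, 0.15) is 0.42.

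| True dropout q | Any dropout (2.10.2.2) | 9 or more of 54 (2.6, dropout alone) |
|---|---|---|
| 5% | 0.94 | 0.001 |
| 10% | 0.997 | 0.09 |
| 15% | 0.9998 | 0.42 |
| 20% | 1.00 | 0.78 |

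With 52 participants and 15% dropout, the figures are 0.9998 and 0.53 (8 or more).

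**Step 2: where the two conditions part.**

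- With 1 to 8 dropouts and no other deviation, section 2.10.2.2 calls for ITT and the section 2.6 condition is not met.
- With 9 or more non-adherent participants and no dropouts, the section 2.6 condition is met and the dropout condition of section 2.10.2.2 is not.
- With 8 retained but non-adherent participants (8/54 = 14.8%) and no dropouts, neither condition is met. Unless the power condition applies, the only analysis called for is per-protocol, which can leave out all 8 although their data exist. This case is unlikely if dropout is near 15%, but it shows what the default permits.

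**Step 3: the power condition.** If power means power computed from the observed effect, 80% corresponds to a fixed p-value:

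- z test: z = 1.960 + 0.842 = 2.80, p = 0.005.
- F test with 1 and 44 df (group effect, 46 − 2 = 44): F = 8.21, p = 0.006.
- F test with 3 and 132 df (group by visit with four visits, 3 × 44 = 132): F = 3.74, p = 0.013.

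On that reading, any p-value above roughly 0.005 to 0.013 would call for ITT, including results that are significant at 0.05. If power instead means power at the retained sample size, the condition does not depend on the outcomes, but it is still undefined.

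**The case against.** **The word primary is not used, and ITT will almost certainly be run.** This stands. Per-protocol gets its standing only from being the sole unconditional analysis. A reader might infer that ITT is a remote fallback; the 0.9998 shows otherwise. The defect is that its status is not fixed.

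**The two conditions are not strictly contradictory.** This also stands. Section 2.6 says if, not only if, and whenever it is met through dropout the other is met too. They are unharmonised rather than logically incompatible, but they still give different instructions in the cases of step 2.

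**Dependence on the result rests on one reading of power.** Correct. A reader might infer that the deciding analysis will be picked from the results. The dropout and adherence conditions turn on conduct, not necessarily on outcomes, and the power condition would seldom be the deciding one because dropout will nearly always have occurred.

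**A bias of stated size is not supported.** A reader might expect the effect to be overstated by some fraction of a standard deviation. That needs assumptions about how leavers differ between arms. The later data of people who leave are also missing under ITT, so such a figure would not be the difference between the two analyses.

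**Section 2.10 may not restrict follow-up.** Its sentence comes straight after the text on halting for signs of infection and may only mean that data gathered before a halt are kept. Read literally, it could exclude the six-month visit, since 24 weeks × 7 = 168 days falls before day 180. That conflicts with the visit schedule in section 2.4, so the sentence is ambiguous rather than shown to be wrong.

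**Section 2.9 does not define the per-protocol set.** It says that "protocol adherence will be measured by calculating the percentage of patients who complete the assessments", but it does not link this to the analysis. Neither that set's definition nor missing-data handling, both commonly left to an analysis plan, is counted here as missing.

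**Conclusion.** The point holds in this form: the article states per-protocol as its only unconditional analysis of a superiority comparison, attaches ITT to two unharmonised conditions, and does not say which result decides the trial. These are stated rules, not details left to a document that is not shown.

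At the protocol's own 15% dropout with 54 participants, the conditions are met with probabilities of about 0.9998 and 0.42, given independent dropout and the 15% reading of section 2.6. Participants who stay but do not adhere can be excluded from the unconditional analysis. The outcome result would itself trigger the switch, at p above roughly 0.005 to 0.013, only if power means observed power. How large any bias would be, and in which direction, cannot be derived from the document.

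**What to change.** 1. In section 2.10.2.2, name one unconditional primary analysis: all randomised participants in their assigned arm, with all EMG data collected, whether or not they adhered to tDCS or rehabilitation.
2. Delete the conditional ITT sentences in sections 2.6 and 2.10.2.2, including the power condition.
3. Keep per-protocol as a sensitivity analysis, with its set defined before unblinding.
4. Preferably replace repeated measures ANOVA with a linear mixed model (arm, visit, arm by visit). The conventional ANOVA drops anyone with a missing visit; the mixed model uses their other visits. Naming the primary set does not depend on this step. Add baseline EMG as a covariate only if a pre-stimulation measurement is confirmed: section 2.4 starts assessments at one month, and the earliest EMG in Table 1 is a post-allocation postsurgical time point.
5. Clarify in section 2.10 that the sentence on information gathered before the intervention ends does not exclude scheduled follow-up.

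The cost is mainly wording, and SPSS can fit the model. Confirming a pre-stimulation EMG means reconciling section 2.4 with Table 1. The downside is that the estimate may be slightly less favourable than the per-protocol one.

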### Study design

2.1

This study will be a randomized controlled trial featuring a double-blind, comparative, and longitudinal approach. To ensure clarity and thoroughness, the study will adhere to the SPIRIT statement guidelines (Table 1) (37). The TIDieR checklist will be used to report outcomes (38). The planned investigation will include a protocol with two comparator arms: NIBS + ProtocolRHB and ShamNIBS + ProtocolRHB, with participants randomly assigned to either arm (Figure 1). Patients will provide written informed consent prior to any study procedure, including randomization. Data collection will be conducted between April 2025 and December 2027. This study was approved by the Ethics Committee of the Catholic University of Valencia (UCV/2023-2024/053). Additionally, the study was pre-registered at https://www.Clinicaltrial.gov on 01/01/2025 (NCT06818201).

**Table 1 T1:** Execution schedule – recruitment, intervention, and reassessment.

	Study period							
	Enrolment	Allocation	Post-allocation					Close-out
Time Point	*-t_1_*	0	*t_1_*	*t_2_*	*t_3_*	*t_4_*	*T_5_*	*t_x_*
Enrolment								
Eligibility screen	X							
Informed consent	X							
Allocation		X						
Interventions								
*[NIBS* *+* *_RHB_]*								
*[SHAM_NIBS_* + _RHB_*]*								
Assessments								
*[Anthropometric data]*	X	X						
*[Psychosocial Assessment]*			X	X	X	X	X.	X
*[Scoring Scale]*			X	X	X	X	X	X
*[Functionality]*					X	X	X	X
*[EGGTMS]*			X		X		X	X
*EMGs*			X		X		X	X

t1, 2024; 0, start study; t1, postsurgical; t2, postsurgical30; t3, postsurgical60; t4, postsurgical90; t5, postsurgical180; tx, study completion.

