### Procedure

2.4

After group assignment, all participants will be assessed at four scheduled time points after surgery: one month (post-surgical30), two months (post-surgical60), three months (post-surgical90), and six months (post-surgical180). Scoring scales and psychosocial assessments will be evaluated at each visit (Figure 1). All assessments will be conducted bilaterally to allow within-subject comparisons.

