Furthermore, the tDCS device from Ionclinics will be used in the study. The device will be applied during the early stage of rehabilitation, specifically during activation, as the exercises required will be less demanding, less intricate, and more appropriate for this intervention. The treatment plan includes 16 sessions over an 8-week period, with two sessions each week. Each session will administer a continuous current of 2 mA for 20 min. The setup comprises two electrodes (a red anode and a black cathode) and two sponge pads with conductive gel, all incorporated into a helmet tailored to the patient. Electrode placement will adhere to the international 10–20 system for tDCS (46). The primary motor cortex (M1) will be the focus of stimulation, with the anode placed at either C3 or C4, corresponding to the hemisphere contralateral to the injured leg, to target the affected motor area. The cathode will be positioned at the opposite supraorbital area, either Fp1 or Fp2. This placement ensures that stimulation is applied to the motor cortex controlling the injured limb, which is critical for modulating cortical excitability and enhancing the neuromuscular control. The tDCS stimulation will be applied prior to this early rehabilitation phase to ensure proper monitoring and to maximize the safety and efficacy of the intervention*.* The tDCS stimulation will be applied prior to this early rehabilitation phase. Specifically, during the Post-Surgery Recovery Phases 1.1 and 1.2, as well as the Strength and Motor Control Phase 2.1.

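### The primary repeated measures ANOVA names no baseline covariate although EMG is scheduled at t1; if t1 precedes stimulation, adjusting for it would recover power at almost no cost

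*Protocol article*

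**What the plan says.** Section 2.10.2.2 fixes the model for all outcomes: "repeated measures ANOVA will be applied, with experimental groups as factors and Bonferroni corrections for" post hoc tests. It adds that "Comparisons within and between groups for both primary and secondary outcomes will assess time, group, and interaction effects". No covariate is named, and none of the three effects is singled out as the decisive test. Section 2.6 sizes the trial on the same type of model.

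Table 1 (section 2.1) marks EMG and EEG/TMS at t1, t3, t5 and tx, and the scoring and psychosocial scales at t1 and every later visit. Its legend reads "t1, postsurgical; t2, postsurgical30; t3, postsurgical60; t4, postsurgical90; t5, postsurgical180; tx, study completion". The t1 column stands under the post-allocation heading.

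Section 2.4 gives a different schedule: "all participants will be assessed at four scheduled time points after surgery: one month (post-surgical30), two months (post-surgical60), three months (post-surgical90), and six months (post-surgical180"). It has no visit before one month. The abstract also speaks of four time points.

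On stimulation, section 2.7.1 places tDCS in the early rehabilitation phases: "Specifically, during the Post-Surgery Recovery Phases 1.1 and 1.2, as well as the Strength and Motor Control Phase 2.1". Table 2 starts Phase 1.1 at week 0. No section says whether the t1 recording comes before the first session.

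**The concern.** A value of the primary outcome taken after surgery but before stimulation is a true baseline. The stated model has only two ways to treat it: as one more level of time, or not at all.

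- **As a level of time.** Randomisation makes the expected arm difference at a pre-stimulation t1 zero. The group main effect averages that zero with the follow-up differences, and a chance imbalance at t1 also enters it. The interaction does use t1 as a reference, but it spreads a sustained shift over 3 degrees of freedom and does not regress on the baseline value.
- **Left out.** Nothing is diluted, but the information in the baseline is discarded.

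With about 23 evaluable athletes per arm, the loss of power could decide whether a real effect is detected. The same holds for the secondary outcomes that have a t1 value.

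**Working it through.** **Inputs from the protocol article.** Section 2.6: "Cohen's effect size was set at 0.357 based on a previous study"; "The calculation incorporated a statistical power of 0.95, an alpha level of 0.05, and two intervention groups"; "A preliminary sample of 46 subjects, divided into two groups of 23 participants each". Table 1: EMG at t1 and three later visits.

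**Assumptions, not in the document.** The 0.357 is Cohen's f, so d = 2 × 0.357 = 0.714 for two groups. Visits have equal variance and a common correlation rho (compound symmetry), with rho 0.3, 0.5 and 0.7 shown. The effect is 0 at t1 and d at each later visit. Tests are at 5%, two-sided for the 1-df contrasts.

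**The plan's own figure.** The 46 cannot be reproduced from the stated inputs, because the number of measurements, the correlation and the tested effect are not given. At rho 0.5 with 2 to 6 measurements, the between-group test needs 80, 70, 66, 64 and 62 in total, and the interaction needs 28, 22, 20, 16 and 16. The figures below therefore take 23 per arm as given.

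**Dilution.** With t1 as one of four levels, the group main effect estimates (0 + d + d + d)/4 = 0.75d. This holds at any correlation.

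**Noncentrality (n = 23 per arm).**
- Group main effect, df 1, 44: (n/2)(0.75d)² / [(1 + 3rho)/4]
- Interaction, df 3, 132: (n/2)(0.75d²) / (1 − rho)
- Mean of three later visits, unadjusted, df 1, 44: (n/2)d² / [(1 + 2rho)/3]
- The same mean adjusted for t1, df 1, 43: (n/2)d² / [(1 + 2rho)/3 − rho²]

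At rho 0.5, (n/2)d² = 11.5 × 0.510 = 5.86. The four values are:
- group: 5.86 × 0.5625 / 0.625 = 5.28
- interaction: 5.86 × 0.75 / 0.5 = 8.79
- unadjusted mean: 5.86 / 0.667 = 8.79
- adjusted mean: 5.86 / 0.417 = 14.07

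**Power from the noncentral F distribution.**

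| Test | rho 0.3 | rho 0.5 | rho 0.7 |
|---|---|---|---|
| Group main effect, t1 included | 73% | 61% | 52% |
| Group-by-time interaction | 53% | 69% | 90% |
| Later-visit mean, unadjusted | 90% | 83% | 75% |
| Later-visit mean, t1-adjusted | 94% | 96% | 99% |

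The last two rows isolate the covariate, which adds about 4, 13 and 23 points. The rest of the gap to the first two rows comes from using a single contrast of the later visits.

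**Weak baseline correlation.** Keep rho 0.5 among the later visits, but let t1 correlate only 0.1 to 0.3 with them. The adjusted mean then has 83% to 88% power, against 83% unadjusted.

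**Fading effect.** Let the effect be d, d/2 and d/4 at the three later visits.

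| Test | rho 0.5 | rho 0.7 |
|---|---|---|
| Interaction | 53% | 78% |
| Later-visit mean, t1-adjusted | 57% | 70% |
| Day-60 contrast, t1-adjusted | 78% | 91% |

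At rho 0.7 the adjusted mean falls below the interaction, while the adjusted day-60 contrast does better than both.

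**The case against.** The strongest reply is that the premise is inferred. Section 2.10.2.2 does not list the levels of time, and section 2.4 has no visit before one month; if that section governs, there may be no t1 EMG at all. Nor is t1 shown to be a baseline: Table 1 puts it after allocation and stimulation belongs to a phase that starts at week 0. Both points stand, so the concern is conditional.

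A reader might infer that the primary analysis is biased toward zero by construction. The document does not support that. Only the group main effect is diluted, and it is not named as the decisive test. The interaction and comparisons at a single visit are not diluted, and a chance t1 imbalance does not enter the interaction as it enters the group effect. A reader might also infer that the interaction is underpowered in general; at rho 0.7 it has 90% under a sustained effect, and the protocol gives no correlation.

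It is also fair to say that a sustained effect is a favourable assumption, since stimulation lasts 8 weeks while EMG continues to day 180 and study completion. The fading-effect figures show how much this matters.

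Finally, a condensed article may leave covariates to an analysis plan that is not shown. The point here is narrower: the article states a model, and a better use of data already scheduled can be named.

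**Conclusion.** The point holds as a conditional efficiency improvement, with moderate confidence. If t1 precedes stimulation, both readings of the stated model use it poorly: as a level of time it shrinks the group main effect to 3/4 of a sustained effect, and if omitted its information is lost. Under the stated assumptions the covariate alone is worth about 4 to 23 points of power for rho 0.3 to 0.7. It is worth 0 to 5 points if t1 is only weakly correlated with later visits.

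The size rests on compound symmetry, on d = 0.714 and on the time course of the effect. No single contrast is best under every time course, so the contrast must be chosen deliberately. Repeated measures ANOVA with a group-by-time test remains a valid analysis.

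**What to change.** 1. Reconcile Table 1 with section 2.4 on whether a t1 visit with EMG exists, and state whether it is taken before the first tDCS or sham session.
2. If it is, change section 2.10.2.2: remove t1 from the outcome vector and fit a linear mixed model or ANCOVA to the later visits with group, visit, group-by-visit and the t1 value as covariate.
3. Prespecify one adjusted between-arm contrast as the decisive test, chosen for the expected time course: for example, the mean of the later visits if the effect should last, or day 60 if it should fade.
4. Use the same model for each secondary outcome with a pre-stimulation t1 value (Lysholm, ACL quality of life, Tampa scale, Pain Catastrophizing Scale, EEG/TMS).

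The cost is one degree of freedom and a change of analysis wording. No further data are needed beyond Table 1, and the stated software, SPSS, can fit the model.
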